### Clinical screening

The PI will arrange a suitable appointment to determine eligibility for inclusion into the study based on a screening questionnaire administered via telephone which will search for evidence of serious spinal pathology and discuss the study protocol and requirements of the participant. The screening questionnaire is adapted from the New Zealand Accident Compensation Corporation (ACC) guidelines [12] which have been designed to detect any potentially significant symptoms of serious spinal pathology. Evidence for such a disorder will exclude the participant from the study.

### Research protocol and timetable

At an initial visit each participant's weight, height, age, sex, occupation and ethnicity will be recorded. Occupation coding will be carried out according to Australian and New Zealand Standard Classification of Occupations [56]. Also recorded, whether the participant is working or off-work due to the current LBP episode, the number of days of the week and total average hours that each participant works, and whether the participant considers their work to be either manual or sedentary. This occupational information will be used to provide a baseline descriptive account of the group, and also included as a potential confounder in the relationship between PA and functional recovery.

Participants will complete a number of validated functional LBP outcome measures at baseline [57]. The primary outcome measure is the RMDQ, accepted as a valid and sensitive measure of condition-specific functional outcome in LBP populations [58], and considered as the preferred instrument for assessing change in function over time in LBP [59]. Secondary outcomes will be the *Visual Analogue Scale *(VAS) measure of pain over the past 7 days which has been shown to be a valid and reliable clinical measure of pain in LBP populations [60] and a specific activity question developed for this study which asks the participant whether they have returned to full "normal' activities since the episode of low back pain (Y/N).

Other measures will investigate for potential confounding factors in the relationship between PA and functional recovery (RMDQ). These are measurements of depression, anxiety, emotional distress and fear avoidance and occupational activity levels and intensity. The *Baecke Questionnaire *(BPAQ) will be used to record the level of PA in the month prior to the current episode of LBP and activity levels at the 1 year point. The BPAQ is a reliable and valid measure of activity in both free living and LBP populations [61,62]. This questionnaire is divided into 3 sections which are individually scored: leisure time index, work index and sports index. The BPAQ work index score will thus provide a measure of the relative intensity of work activities [63] and occupational activity levels [64]. Fear avoidance beliefs will be measured with the *Fear-Avoidance Beliefs Questionnaire *(FABQ); a reliable measure of pain-related fear in acute LBP [65] and a valid measure for functional disability in acute and chronic LBP populations [66,67]. The 12-item *General Health Questionnaire *(GHQ12) will be used as a validated measure for evaluating levels of anxiety and depression in the general population [68].

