## Analyses

Multiple linear regression will be used to investigate the associations of the main predictor variable, change in RT3 VM counts/hour/week (ΔRT3) from baseline to 3 months, with the main outcome variable change in functional outcome (ΔRMDQ). The change score will be calculated by subtracting each participant's 3 month RMDQ score from their baseline RMDQ score. Unadjusted and adjusted analyses will be performed. Adjusted analyses will include the following variables, shown to be putatively associated with both PA and functional recovery in LBP: age, gender, occupation, baseline pain level (pain questionnaire), functional status (baseline RMDQ) and baseline measurements of depression, anxiety, emotional distress and fear avoidance (GHQ12 and FABQ). We plan to analyze each of the explanatory variables univariately initially to assess the relationship with the dependant variable (RMDQ change). We will include factors in the model which in univariate analyses have a *p*-value < 0.10. The significant explanatory variables contained in the separate models will then be combined and re-examined using further modeling. We plan to use multiple linear regression to assess which of the included explanatory variables and/or their interactions with PA change predict change in RMDQ. For those variables which remain in the final model, an examination of their significance (p < 0.05) will be undertaken to evaluate their contribution to the final model.

At 1 year the relationship between ΔRT3 and presence or absence of on-going low back pain (Y/N) from the modified Nordic LBP questionnaire will be investigated using logistic regression. At 1 year the relationship between the BPAQ change score from baseline (pre-LBP) to BPAQ score at 1 year (ΔBPAQ) with the outcome of on-going LBP (Y/N) will also be explored using logistic regression.

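### The pre-episode Baecke leisure and sport scores are collected but enter neither ΔRT3 model, although usual activity could plausibly confound the ΔRT3 slope

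*Protocol article*

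**What the plan says.** **What is collected** (Research protocol and timetable). The paragraph on further measures opens: "Other measures will investigate for potential confounding factors in the relationship between PA and functional recovery (RMDQ"). It then names them: "These are measurements of depression, anxiety, emotional distress and fear avoidance and occupational activity levels and intensity". The BPAQ is introduced in the same paragraph. It "will be used to record the level of PA in the month prior to the current episode of LBP", is repeated at 1 year, and is "individually scored: leisure time index, work index and sports index". The work index is the only one of the three that the paragraph ties to a listed confounder, namely occupational activity.

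**What is modelled** (Analyses). The main predictor is "change in RT3 VM counts/hour/week (ΔRT3) from baseline to 3 months". For the 3-month outcome: "Adjusted analyses will include the following variables, shown to be putatively associated with both PA and functional recovery in LBP: age, gender, occupation". The list continues with baseline pain, baseline RMDQ and "baseline measurements of depression, anxiety, emotional distress and fear avoidance (GHQ12 and FABQ"). It contains no BPAQ index and no baseline RT3 level. A univariate screen at p < 0.10 governs which factors enter. The 1-year logistic model of ongoing pain on ΔRT3 lists no covariates. The pre-episode BPAQ appears once, within ΔBPAQ, which is the exposure in a separate 1-year logistic model.

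**The concern.** ΔRT3 is an absolute difference in average counts per hour (Data management; Analyses). Suppose two people both go from 70% to 95% of their own usual activity. If one is normally twice as active as the other, that person's ΔRT3 is twice as large for the same degree of return. Where activity falls and recovers in proportion like this, ΔRT3 carries information about how active someone usually is as well as about how far they have come back.

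That matters if usual activity also bears on recovery. The Background cites studies in which exercise outside work tended to protect against recurrence, leisure activity predicted return to work, and the most active in leisure time had lower odds of back disability. The Analyses section chooses covariates on putative association with both activity and recovery, and usual activity meets that standard. A positive ΔRT3 slope could then partly mean that habitually active people recover better. The Abstract's discussion says the results will bear on guidelines that recommend restoring normal activity, which is a different claim. The BPAQ is the only measure of pre-onset activity that the article describes, so leaving it out removes an available check.

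**Working it through.** **1. Text check.** Pre-episode leisure and sport indices are in neither of the two ΔRT3 models (3-month linear, 1-year logistic). They appear only inside ΔBPAQ. The 3-month list is written out, so its content is a stated choice. The 1-year model's lack of covariates may reflect condensation for the article.

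**2. Inputs for the size of the problem.** The plan gives no figure on this point to reproduce. From Sample size and statistical power: n = 65 analysed and two-sided α = 0.05. The 65 is taken as stated; 120 recruits with 40–50% loss leave 72 to 60. Everything else is assumed:
- U, usual activity, has a between-person coefficient of variation (CV) of 0.2–0.5.
- The share of usual activity has mean 0.70 (SD 0.15) at baseline and mean 0.95 (SD 0.12) at 3 months, independent of U and of each other.
- U correlates ρ = 0.2–0.4 with recovery.
- Restoration itself has no effect.

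**3. Proportional case.** ΔRT3 = U × D, where D is the change in share. D has mean 0.95 − 0.70 = 0.25 and variance 0.15² + 0.12² = 0.0369. With U scaled to mean 1:

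Var(ΔRT3) = (1 + CV²)(0.0369 + 0.0625) − 0.0625

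corr(ΔRT3, U) = 0.25 × CV / √Var(ΔRT3)

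corr(ΔRT3, D) = √0.0369 / √Var(ΔRT3)

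At CV 0.2, Var = 1.04 × 0.0994 − 0.0625 = 0.0409, so corr(ΔRT3, U) = 0.05/0.202 = 0.25. At CV 0.5, Var = 1.25 × 0.0994 − 0.0625 = 0.0618, so corr(ΔRT3, U) = 0.125/0.2485 = 0.50.

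The spurious correlation with recovery is ρ × corr(ΔRT3, U). The chance of significance uses Fisher's z, with m = atanh(r) × √62: Φ(m − 1.96) + Φ(−m − 1.96).

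| CV | corr(ΔRT3, D) | corr(ΔRT3, U) | spurious r, ρ = 0.2 / 0.4 | chance of p < 0.05 |
|---|---|---|---|---|
| 0.2 | 0.95 | 0.25 | 0.05 / 0.10 | 7% / 12% |
| 0.3 | 0.90 | 0.35 | 0.07 / 0.14 | 9% / 20% |
| 0.4 | 0.84 | 0.44 | 0.09 / 0.17 | 11% / 28% |
| 0.5 | 0.77 | 0.50 | 0.10 / 0.20 | 12% / 36% |

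For the last cell, atanh(0.201) × √62 ≈ 1.61 and Φ(1.61 − 1.96) ≈ 0.36. With U lognormal and ρ defined on log U, the same corner gives r = 0.19 and 33%, hence about 35%. With ρ = 0.1 the chance is 5.4–6.8%.

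**4. Additive case.** If everyone's activity drops and rebounds by an amount unrelated to U, U cancels from the within-person difference. Then corr(ΔRT3, U) = 0 and the chance is 5%.

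**5. On the RMDQ scale.** A second simulation assumed CV 0.2–0.4, mean share 0.65 rising to 0.95, baseline-share SD 0.15–0.25 with half that at 3 months, ρ 0.2–0.3, and the plan's SD of 5.4. It gave a spurious slope of 0.23–0.90 points per SD of ΔRT3. The difference between the top quartile of ΔRT3 and the rest was 0.6–1.7 points, against the plan's 4-point target. Adding true U brought the slope to about zero.

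**The case against.** **The protocol does not contradict itself.** A reader might infer that it names pre-episode activity as a confounder and then forgets it, because the BPAQ sits in the paragraph on confounders. The text does not support that. The named confounders are psychological and occupational, as in the second hypothesis, and the BPAQ's stated purpose of recording activity before the episode and at 1 year is met by ΔBPAQ. This stands.

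**The mixing is not built into ΔRT3.** A change score removes any additive usual level. Proportional fall and rebound is plausible for activity counts, but the protocol does not state or show it. This stands, and it is why the range must start at 5%.

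**The evidence for confounding is mixed.** The Background also cites a review that did not find activity level to predict return to work and a five-year follow-up with no apparent benefit of regular exercise, and it calls the overall evidence equivocal. Usual activity cannot be called an established common cause. It still meets the protocol's own, looser, criterion of putative association.

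**The figures are for an unadjusted correlation.** The listed covariates could absorb part of any link between usual activity and recovery. This stands. The upper end also needs CV 0.5, ρ = 0.4 and full proportionality together.

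**Return to normal is handled elsewhere**, by the third objective and a yes/no item. That is so, but a yes/no item does not show what drives the ΔRT3 slope.

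**The remedy is partial.** If the recalled BPAQ correlates 0.3–0.5 with true usual activity (assumed), adjusting for it in the extreme case lowers the spurious correlation only from 0.20 to 0.19–0.16, and the chance of significance from 36% to about 32–25%. Nor can one say that baseline RT3 is useless as a proxy: in the proportional model it correlates 0.68–0.90 with usual level. It is not in the list either. These points limit the gain but do not remove the gap.

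**Conclusion.** The concern holds as an omission from the stated models. A measure of pre-episode leisure and sport activity is already collected, meets the plan's own criterion for a covariate, and is used in neither ΔRT3 model. The resulting bias is possible but not demonstrated. Under the assumptions above, the chance of a spurious significant ΔRT3 result at n = 65 lies between 5% (additive change, no bias) and about 35% (extreme proportional case, before other covariates). The documents give no figure for the spread of usual activity, its link to recovery or the form of the rebound, so the position within that range is unknown. They do not support the stronger readings that ΔRT3 necessarily reflects usual activity or that usual activity is shown to cause recovery. The change is worth making because it is cheap and tests the interpretation of the main association.

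**What to change.** In Analyses, pre-specify the pre-LBP BPAQ leisure-time and sports indices as additional covariates in the 3-month linear model and the 1-year logistic model for ΔRT3. State that they are exempt from the p < 0.10 screen. Report the ΔRT3 slope with and without them, fitted to the same participants so that missing questionnaires do not drive the difference. In the logistic model, note that an odds ratio can shift when a predictive covariate is added even without confounding.

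**Cost.** A line or two of text and no new data. Two more terms are fitted in a small sample, alongside an already long covariate list. Control is partial, because the BPAQ is recalled after onset and is on a different scale from RT3 counts. An unchanged slope would therefore be reassuring but would not exclude confounding.

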### Physical activity measurement

All RT3 monitors will undergo testing prior to field use as part of the standardised protocol recommended when employing accelerometry measurement [69,70]. Previous research has shown high levels intra-monitor variability [49] and therefore each participant will be required to use the same RT3 monitor at baseline and 3 months. Field practice of monitor use and monitor placement will be standardised by asking the participants to wear the RT3 monitor on the right hip for all waking hours; to report wear times and reason for removal; to note the days that they work; and also to report sleep patterns [70] and hourly activities in an activity diary over the week [53].

The dimensions and specifics of the RT3 have been reported previously [49]. The RT3 triaxial accelerometer stores accumulated activity counts, derived from the three axes ([X^2 ^+ Y^2 ^+ Z^2^]^0.5^) to calculate a summed VM. Mode 4 will be employed for this study, which stores accumulated activity counts every second and calculates an average VM for each one-minute epoch over the 7 days of monitoring. Previous research has validated the use of RT3 VM counts as a measure of free living activity and energy expenditure [50].

Participants will be contacted twice during this week by text and/or phone to improve compliance in wearing the RT3, recording activity in the activity dairy, and to address any problems the participants might be having with either the RT3 or in using the activity diary. At the completion of the week the RT3 data will be downloaded to a portable computer and each participant will complete a 7-day recall questionnaire (7D-PAR) [71,72]. The 7D-PAR provides an estimate of the average total daily energy expenditure (TDEE) and physical activity energy expenditure (PAEE) for each participant.

All participants will be sent a reminder letter between the first and second period of monitoring; further contact will be made approximately 1 week prior to their scheduled date for re-monitoring at the 3-month point. Each participant will then repeat the activity monitoring procedure as per the baseline. At completion of week 12 each participant will be asked to complete the RMDQ, VAS and simple activity question and in addition an RT3 utility questionnaire developed for this study. This will assess any specific utility issues of PA measurement within this patient population.

At 1 year each participant will be sent the following questionnaires: VAS, FABQ, RMDQ, the BPAQ, GHQ12 and a modified Nordic LBP Questionnaire [73] with a self return envelope. The Nordic LBP Questionnaire has been previously employed as a measure of LBP recovery in an occupational setting [74] and as a measure of incident LBP, for assessing the associations between physical activity and incidence of LBP [75]. The BPAQ will be used to record current levels of PA at the 1 year point. The estimated duration of the study will be approximately two years to complete recruitment and 1 year follow-up (Figure 1).

**Figure 1 F1:**
[figure not shown]
**Outline of study protocol**. *At each time point data on low back pain and functional recovery will be collected. † At baseline data on occupational, psychological and behavioural factors collected

### Data management

Following collection, data will be checked for accuracy and completeness and will involve:

• Download of all accelerometry data via StayHealthy^tm ^software into an Excel database.

• A visual review of all accelerometer data to determine the number of days of accelerometer data and to determine whether this satisfies the research protocol criteria.

The downloaded accelerometry data will be checked to ensure that the number of days of accelerometer data matched the protocol, to ascertain sleep times, and to identify possible RT3 malfunctions [76]. Data will then be scanned for nonworn periods. Such data will be set to 'missing' [70]. The data will then be separated into weekdays and weekend days. The sum of RT3 activity counts for each day will be calculated as well as the total number of hours of activity data collected each day. Total weekly activity count will then be divided by the total number of hours worn from each valid day of data collection [76]. The total RT3 score for the 7 days of activity monitoring will be expressed as average VM counts/hour/week. Estimates of data loss and the reasons for any physical activity data loss will also be investigated and a sensitivity analysis performed to investigate the effect of wear time on the relationship between activity change and RMDQ [77].

### Sample size and statistical power

We calculated sample size based upon the detection of a difference in change in RMDQ from baseline to three months in two groups classified as high changers in PA and low changers, as defined by the upper quartile of change in PA. This is a simplification of the actual analysis, but is conservative. The sample size is calculated for 80% power at a two-sided type I error rate of 0.05. Assuming a standard deviation of change in RMDQ score of 5.4 over a 3 month period, [78,79] the detection of a clinically meaningful change of 4 points in the RMDQ score from week 1 to week 12 [55,80], and an assumption of unequal group sizes, the required sample size is 65 participants. Previous research employing the RT3 in free living has found loss of data due to technical issues including monitor malfunction to be a significant issue [81,82]. Therefore a reasonably high attrition rate and potential dropout rate of 40-50% will be used over the 3 time points and this requires data from approximately 120 participants to be collected (Figure 1).

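### The stated requirement of 65 does not follow from the upper-quartile split: the protocol's own inputs give 77 to 80, and 65 gives about 72-73% power for that two-group comparison

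*Protocol article*

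**What the plan says.** All the inputs are in the section Sample size and statistical power of the protocol article.

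- Comparison: change in RMDQ from baseline to three months between "two groups classified as high changers in PA and low changers, as defined by the upper quartile of change in PA".
- Error rates: "The sample size is calculated for 80% power at a two-sided type I error rate of 0.05".
- Variability: "Assuming a standard deviation of change in RMDQ score of 5.4 over a 3 month period".
- Effect: "the detection of a clinically meaningful change of 4 points in the RMDQ score from week 1 to week 12".
- Result: with "an assumption of unequal group sizes, the required sample size is 65 participants".
- Loss: "a reasonably high attrition rate and potential dropout rate of 40-50% will be used over the 3 time points".
- Recruitment target: about 120, set to allow for that loss.

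The section adds that the two-group comparison simplifies the real analysis and is conservative. The Analyses section confirms that the real analysis is different: a linear regression of RMDQ change on change in RT3 counts as a continuous variable.

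**The concern.** No numeric allocation ratio is printed, but none is needed: an upper quartile against the remainder is 25% against 75%, or 1:3. A split that uneven costs a good deal of efficiency relative to equal groups, and 65 looked too small to carry that cost.

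The two-group calculation is the only numerical support given for the size of the study; the article states no power for the regression. If its result does not follow from its inputs, readers are given a required number and a power that the described comparison does not have, and nobody can tell which of the printed elements is the mistaken one.

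**Working it through.** **Inputs** (all from Sample size and statistical power): difference d = 4; SD s = 5.4; two-sided alpha 0.05 (z = 1.960); power 80% (z = 0.842); proportion in the smaller group p = 0.25, from the quartile definition.

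**Formula** for the total number, normal approximation:

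N = (1.960 + 0.842)² × s² / [p(1 − p) × d²]

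The numerator is 7.849 × 29.16 = 228.9.

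**Trying to reproduce 65**

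| Split | p(1 − p) × 16 | N (normal) |
|---|---|---|
| 1:1 | 4.000 | 57.2 |
| 1:2 (upper third) | 3.556 | 64.4 |
| 1:3 (upper quartile, as stated) | 3.000 | 76.3 |

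The stated split gives 77 after rounding up. In whole 1:3 groups it is 20 + 60 = 80, where the t test has 81% power. The printed 65 agrees with an upper-third split.

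**Power at 65 with the stated split.** The standardised difference is 4 × √(65 × 0.1875) / 5.4 = 2.586, and 2.586 − 1.960 = 0.626, which is 73% power. The noncentral t distribution gives 72%. With whole groups of 16 and 49 the values are 73% (normal) and 72% (t), and the difference detectable with 80% power is about 4.4 points (normal), not 4.

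**Other readings of the inputs**

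- *5.4 as the SD of the whole cohort.* The within-group variance is then 5.4² − 0.1875 × 4² = 29.16 − 3 = 26.16, so the within-group SD is 5.11. N = 7.849 × 26.16 / 3 = 68.4, so 69 (71 by the t test, 72 in whole 1:3 groups). Power at 65 is 76-78%, depending on rounding of groups and on normal or t.
- *One-sided alpha 0.05.* The 1:3 split then gives 60.1, or 16 + 48 = 64 in whole groups. This comes close to 65 but contradicts the two-sided test that the section states.

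**Power after loss from 120 recruited, 25:75 split, s = 5.4 within groups**

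| Loss | Evaluable | Groups | Power, normal | Power, t |
|---|---|---|---|---|
| 40% | 120 × 0.60 = 72 | 18:54 | 78% | 77% |
| 50% | 120 × 0.50 = 60 | 15:45 | 70% | 69% |

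**The step from 65 to 120.** 65/0.60 = 108.3, 65/0.55 = 118.2 and 65/0.50 = 130. So 120 corresponds to roughly 45% loss, the middle of the stated range.

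**The case against.** The strongest reply is that no one will run the quartile comparison. The planned test uses activity change as a continuous predictor, and the protocol itself calls the split conservative. That remark can be checked under two assumptions that the document does not state: activity change is normally distributed, and its relation to RMDQ change is linear. The upper-quartile mean then lies 1.695 SD above the mean of the rest, so a 4-point gap means 4/1.695 = 2.36 points per SD of activity change. This is a correlation of 0.42 (5.4 as within-group SD, overall SD 5.67) to 0.44 (5.4 as overall SD). By Fisher's transformation, 80% power needs about 39 to 43 participants, and unadjusted power is about 92-94% at 60. Covariate adjustment, non-linearity or measurement error in the RT3 would lower this, but the margin is wide. This part of the reply stands. A reader might infer that a null result would come from an underpowered study; for the planned regression, the document does not support that.

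Two further replies also stand.

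- The 40-50% loss is stated over all three time points, whereas the powered endpoint needs only baseline and 3 months. Power of 69-70% is therefore a worst case.
- A reader might infer that the inflation to 120 is itself an arithmetic failure, because 50% loss would need 130. But the target is given as approximate for a range of losses, and it fits the middle of that range.

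The ambiguity over the SD narrows the gap without closing it. On the whole-cohort reading the requirement is 69 rather than 77, and 72 evaluable participants would give 81-82% power.

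None of these replies makes 65 follow from the stated inputs. Calling a calculation conservative describes its relation to another analysis; it does not change the result of the calculation.

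**Conclusion.** The point holds as a correction of stated figures. With the upper-quartile split and the other inputs as printed, the requirement is 77 (normal) or 80 (t, 20:60), against 65 stated: a shortfall of 12 to 15 participants. Power at 65 is about 72-73%, against 80% stated. These figures take 5.4 as the within-group SD; on the whole-cohort reading they become 69 and 76-78%, so 65 is too low on either reading.

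That 65 came from an upper-third split is an inference from the match with 64.4. The document does not say so, and the mismatch does not depend on it. Nothing here shows that the planned regression lacks power or that 120 is too few to recruit, so this is a reporting correction and not a fault in the design.

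**What to change.** Keep the recruitment target of 120 and correct the text in one of two ways.

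1. Keep the upper-quartile definition, print the 25:75 ratio, and state the requirement as 77 (80 by the t test in whole groups). Give the power of the two-group comparison as about 77-78% with 72 evaluable (40% loss) and, as the worst case, 69-70% with 60 evaluable (50% loss, which the protocol counts over all three time points and not only to 3 months).
2. If another split was used, state it in place of the upper quartile. Should it prove to be an upper third, 65 stands by the normal approximation, and 60 evaluable (20:40) would give 77% (normal) or 76% (t).

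In either case add three clarifications: whether 5.4 is a within-group or whole-cohort SD; that the power refers to the simplified two-group comparison, with the planned regression on continuous activity change expected to be more powerful; and that 120 corresponds to about 45% loss from 65, while 50% would need 130.

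The cost is a few sentences. No extra participants and no change to the analysis are needed; under the first option the stated power becomes somewhat less favourable.
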